# Effects of acupuncture synchronized rehabilitation therapy on upper limb motor and sensory function after stroke: a study protocol for a single-center, 2 × 2 factorial design, randomized controlled trial

**DOI:** 10.3389/fneur.2023.1162168

**Published:** 2023-09-28

**Keywords:** stroke, upper limb, acupuncture synchronized rehabilitation therapy, motor function, sensory function, activities of daily living, factorial design, randomized controlled trial

## Abstract

**Background:**

Upper limb function reconstruction has been an important issue in the field of stroke rehabilitation. Due to the complexity of upper extremity dysfunction in stroke patients, the clinical efficacy produced by central or peripheral stimulation alone is limited. For this reason, our group has proposed acupuncture synchronized rehabilitation therapy (ASRT), i.e., simultaneous scalp acupuncture and intradermal acupuncture during rehabilitation. Pre-experiments results showed that this therapy can effectively improve the motor and sensory functions of upper limbs in post-stroke patients, but the clinical efficacy and safety of ASRT need to be further verified, and whether there is a synergistic effect between scalp acupuncture and intradermal acupuncture also needs to be studied in depth. Therefore, we designed a randomized controlled trial to compare the efficacy and safety of different therapies to explore a more scientific “synchronous treatment model.”

**Methods:**

This is a single-center, randomized controlled trial using a 2 × 2 factorial design. We will recruit 136 stroke survivors with upper extremity dysfunction and randomize them into four groups (*n* = 34). All subjects will undergo routine treatment, based on which the Experimental Group 1: rehabilitation training synchronized with intradermal acupuncture treatment of the affected upper limb; Experimental Group 2: rehabilitation training of the affected upper limb synchronized with focal-side scalp acupuncture treatment, and Experimental Group 3: rehabilitation training synchronized with intradermal acupuncture treatment of the affected upper limb synchronized with focal-side scalp acupuncture treatment; Control Group: rehabilitation training of the affected upper limb only. The intervention will last for 4 weeks, 5 times a week. Both acupuncture treatments will be performed according to the Revised Standards for Reporting Interventions in Clinical Trials of Acupuncture (STRICTA). The primary outcome indicators for this trial are Fugl-Meyer Assessment-Upper Extremity and Somatosensory Evoked Potential. Secondary outcome indicators include Wolf Motor Function Test, Upper Extremity Function Test, revised Nottingham Sensory Assessment Scale, Diffusion Tensor Imaging, and Modified Barthel Index. The incidence of adverse events will be used as the indicator of safety.

**Discussion:**

The study will provide high-quality clinical evidence on whether ASRT improves upper limb motor and sensory function and activities of daily living (ADL) in stroke patients, and determine whether scalp acupuncture and intradermal acupuncture have synergistic effects.

**Clinical trial registration:**

https://www.chictr.org.cn/, Chinese Clinical Trial Registry [ChiCTR2200066646].

## 1. Introduction

Stroke, also known as cerebrovascular accident, is currently the second leading cause of disability worldwide and is characterized by high morbidity and disability rate (1, 2). Thanks to continuous advances in various diagnoses and treatment techniques, the mortality rate of stroke patients has decreased in recent years (3). However, increased survival of stroke patients has also heralded an increase in chronic stroke patients (4), and most surviving stroke patients tend to have varying degrees of dysfunction left over (5). The lack of function obviously reduces their quality of life and imposes a considerable burden on their families and society.

Studies have shown that 65% of patients have residual upper Extremity dysfunction 6 months after stroke occurred (6). The function of upper limb is closely related to ADL, and that persistent non-recovery of the hand and upper limb function is a major impediment to returning to home and work (7). In addition, the upper extremity function is more delicate and complex, and involves more central parts of the brain, making it more difficult to recover (8–10). Therefore, the reconstruction of upper limb function has been an important subject in the field of stroke rehabilitation.

In recent years, several experiments have pointed out that rehabilitation during scalp acupuncture with needle retention is more effective than rehabilitation after scalp acupuncture in enhancing the upper extremity function of stroke patients, suggesting that the effects of both may not simply be additive (11, 12). To further investigate this issue, our research team conducted a systematic evaluation using Meta-analysis, and the results showed that the simultaneous treatment improved the FMA and MBI scores of stroke patients significantly compared to conventional acupuncture combined with rehabilitation and that this “synchronized treatment mode” better mobilized the neurofeedback mechanism, and thus help patients to establish normal motor patterns and ADL ability (13).

Currently, “simultaneous treatment modalities” of acupuncture and rehabilitation are commonly used in clinical practice including intradermal acupuncture synchronized rehabilitation and scalp acupuncture synchronized rehabilitation, both of which have been clinically verified (14, 15). Intradermal acupuncture stimulates peripheral acupoints to transmit nociceptive sensation to the brain and produce motor response after information integration, thus improving patients' movement function (16); while scalp acupuncture can strengthen sensory integration by directly stimulating local brain areas, thus regulating motor function (17). However, upper limb dysfunction after stroke is extremely complex, and the clinical efficacy produced by considering local stimulation such as central or peripheral alone is limited. Previous research has shown that there is a strong connection between neuroplasticity theory and Traditional Chinese Medicine (TCM) theory (18). Therefore, our research team applied the holistic concept of TCM to stroke rehabilitation, and after reviewing a large amount of literature and based on our previous clinical practice, then proposed Acupuncture Synchronized Rehabilitation Therapy (ASRT), which is one of the “simultaneous treatment modalities,” featuring both head and limb acupuncture, i.e., simultaneous scalp acupuncture and intradermal acupuncture during rehabilitation training, to maximize the activation of nerve conduction pathways, promote neurological remodeling and improve patient function. However, the clinical efficacy and safety of this therapy need to be further verified. In addition, whether there are synergistic effects between the head needle and the intradermal needle need to be further investigated.

Given this, we designed this clinical randomized controlled trial to compare the efficacy and safety of upper limb rehabilitation training with intradermal acupuncture therapy or scalp acupuncture therapy or all three at the same time (i.e., ASRT) and upper limb rehabilitation training alone, to explore a more scientific and rational treatment model, so as to establish a new and efficient stroke rehabilitation program. In this study, we will establish a scientific basis for the rehabilitation of stroke-related upper limb dysfunction.

## 2. Methods

### 2.1. Study design

This is a prospective, open, single-center, randomized controlled trial using a 2 × 2 factorial design. The two trial factors are the head needle and intradermal needle, each with two levels (with and without). Both intradermal acupuncture and scalp acupuncture are designed on the basis of the standard Revised Standards for Reporting Interventions in Clinical Trials of Acupuncture (STRICTA) (19). The study will include 136 stroke patients with upper limb dysfunction, grouped into four groups of 34. All subjects will undergo routine treatment, based on which the Experimental Group 1 (EG1): rehabilitation training synchronized with intradermal acupuncture treatment of the affected upper limb; Experimental Group 2 (EG2): rehabilitation training of the affected upper limb synchronized with focal-side scalp acupuncture treatment, and Experimental Group 3 (EG3): rehabilitation training synchronized with intradermal acupuncture treatment of the affected upper limb synchronized with focal-side scalp acupuncture treatment; Control Group (CG): rehabilitation training of the affected upper limb only. Head and intradermal needling will be performed in accordance with the Chinese national standard GB/T 21709.2-2021 (20) and the fifth edition of Science of Acupuncture and Moxibustion (21). Outcomes will be measured at baseline and a total of five time points at 2 weeks, 4 weeks, 3 months, and 6 months after treatment. Description of the protocol is shown in Table 1, and the study flow chart is presented in Figure 1.

**Table 1 T1:** SPIRIT figure.

	**Study period**						
	**Screening**	**Baseline**	**Treatment**			**Follow up**	
**Time point**	**-t** _1_	**0**	**t** _1_	**t** _2_	**t** _3_	**t** _4_	**t** _5_
**Enrollment**							
Eligibility screen	√						
Informed consent	√						
Demographic information	√						
Medical history	√						
Random allocation		√					
**Interventions**							
Experimental group 1							
Experimental group 2							
Experimental group 3							
Control group							
**Assessments**							
FMA-UE		√		√	√	√	√
SEP		√			√		
WMFT		√		√	√	√	√
UEFT		√		√	√	√	√
reNSA		√		√	√	√	√
DTI		√			√		
MBI		√		√	√	√	√
Adverse events			√	√	√	√	√

-t_1_, patient screening; 0, baseline evaluation; t_1_, time of the start of treatment; t_2_, 2 weeks after treatment; t_3_, 4 weeks after treatment; t_4_, 3 months after treatment; t_5_, 6 months after treatment; FMA-UE, Fugl-Meyer Assessment-Upper Extremity; SEP, Somatosensory Evoked Potential; WMFT, Wolf Motor Function Test; UEFT, Upper Extremity Function Test; reNSA, revised Nottingham Sensory Assessment scale; DTI, Diffusion Tensor Imaging; MBI, Modified Barthel Index.

**Figure 1 F1:**
[figure not shown]
Trial flow chart.

This study protocol was approved by the Ethics Committee of the Affiliated Hospital of Shandong University of Traditional Chinese Medicine (approval No. 2022-080-KY) on August 5, 2022, and this trial was registered with the Chinese Clinical Trial Registry (registration No: ChiCTR2200066646; date: December 12, 2022). This trial will be conducted in accordance with the Standard Protocol Items: Recommendations for Intervention Trials (SPIRIT) checklist (22).

### 2.2. Participant recruitment

The subjects will be hospitalized in the Rehabilitation Department of the Affiliated Hospital of Shandong University of Traditional Chinese Medicine. This department focuses on improving various functional impairments that occur after stroke through a combination of Chinese and Western medicine rehabilitation. Patients will be recruited by distributing brochures in the hospital, posting notices on bulletin boards, and publishing information on the WeChat public platform. Stroke patients who pass the eligibility screening will become subjects of this study. The research team will provide professional treatment for the subjects, and save the cost of instrument examination and scale evaluation. However, medication, rehabilitation, and acupuncture treatments are not free of charge. Patients interested in participating in this trial can contact the researchers by telephone or WeChat. Participation in the trial is voluntary and patients will be encouraged to ask the researcher as many questions as possible before they decide to participate until they fully understand the content, risks, and benefits of the trial. Details such as gender, age, duration of illness, type of stroke, side of hemiparesis, Brunnstrom stage, and Mini-mental state examination (MMSE) score will be recorded by the investigator on their respective Case Report Forms (CRFs) at the time of admission. During treatment, the researchers will collect and monitor the patient's scale assessment report, imaging, and electrophysiological data.

#### 2.2.1. Inclusion criteria

(1) Diagnosis by cranial CT and MRI and meeting the diagnostic criteria for stroke in Chinese Diagnostic Points for Various Types of Cerebrovascular Diseases 2019 (23); (2) The type of stroke is cerebral hemorrhage or cerebral infarction, all of which were unilateral limb hemiparesis with the first onset within 12 months; (3) The duration of the disease was 2 weeks-6 months after onset, with Brunnstrom stage II-IV of the upper limb; (4) Stable vital signs and no further progression of neurological symptoms; (5) Clear consciousness, MMSE > 17 points; (6) Patients aged 18–70 years, of any gender, without serious cardiac, cerebral, or renal complications; (7) Fully informed and voluntary participation in the study, cooperation with assessment and treatment, and signed informed consent form.

Patients who fulfill all of the conditions listed above will be considered for inclusion.

#### 2.2.2. Exclusion criteria

(1) Spatial neglect and severe visual, hearing, intellectual, and attention deficits; (2) Severe upper extremity spasticity with a modified Ashworth scale grading of ≥3; (3) Patients with a previous severe neurological disease or history of psychiatric disorders; (4) Presence of musculoskeletal joint disorders (e.g., fractures, arthritis, etc.) or neurological disorders (e.g., tremor, peripheral nerve injury, etc.) that affect the motor or sensory function of the affected upper extremity; (5) Other reasons for inability to cooperate with training or poor compliance; (6) Those who cannot tolerate head or intradermal needle treatment; (7) Unable to complete DTI or SEP testing; (8) Patients who have received relevant treatment may affect the efficacy observation index.

Patients with any of the above conditions will be excluded.

#### 2.2.3. Withdrawal criteria

(1) Patient-initiated withdrawal; (2) Patients who have certain complications or comorbidities during the trial and are not suitable to continue the trial; (3) The patient's condition deteriorates or another stroke occurs and a dangerous event may occur by continuing the trial.

#### 2.2.4. Termination criteria

The principal investigator has the right to cease the study at any time for reasons including, but not limited to, that continuing the study may harm the rights and interests of some subjects.

### 2.3. Randomization, allocation concealment, and blinding

In this study, a stratified blocked randomization method will be used to stratify patients by age (18–45 years old, 46–75 years old) and type of stroke (cerebral hemorrhage, cerebral ischemia), and SPSS 26.0 software (IBM, Armonk, NY, USA) will be used to stratify and randomize 136 patients who met the criteria for upper limb dysfunction after stroke. The patients will be randomly divided into EG1, EG2, EG3, and CG in a ratio of 1:1:1:1, with 34 patients in each group. The personnel responsible for randomization will not be involved in the process of patient recruitment, treatment, assessment, data collection, and statistical analysis. The grouping results will be placed in sealed, opaque envelopes. Subjects will be numbered according to the time of enrollment, and the appropriate envelopes will be given to the person performing the study intervention according to the number.

To exclude as much bias as possible, the assessors and statistical analysts will be blinded, with 2 assessors who are professionally and uniformly trained and 2 other staff members who are responsible for entering and analyzing the data, regardless of patient assignment and without contact with treatment staff.

### 2.4. Sample size

This study is a RCT with a 2×2 factorial design in which the FMA-UE scores of stroke patients were used as the primary outcome indicators. Based on the results of the preliminary pre-experiment and combined with the relevant literature (24), we used PASS15.0 software (PASS, Kaysville, UT, USA) for sample size estimation. Based on previous studies, we were informed that the mean values of FMA-UE scores after treatment for the four groups were 41.36, 48.21, 52.87, and 40.54, respectively. After calculation, the standard deviation of the two-factor interaction was 0.96, and the estimate of the overall standard deviation was 3.38. The test level was set at α = 0.05 (bilateral test) with a certainty of 1-β = 0.9. The sample size required was 34 cases in each group, and a total of at least 136 patients needed to be included, according to 1:1:1:1 parallel grouping, taking into account the 10% dropout rate of the study population.

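### The planned 34 per group (136) is the number needed for 90% interaction power with no dropout, so it does not contain the 10% allowance the protocol claims

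*Protocol article*

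**What the plan says.** Section 2.4 (Sample size) describes "a 2×2 factorial design in which the FMA-UE scores of stroke patients were used as the primary outcome indicators". It gives these inputs:

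- Means: "the mean values of FMA-UE scores after treatment for the four groups were 41.36, 48.21, 52.87, and 40.54, respectively".
- Effect and spread: "the standard deviation of the two-factor interaction was 0.96, and the estimate of the overall standard deviation was 3.38".
- Test level: two-sided alpha of 0.05.
- Power: 0.9.
- Allocation: 1:1:1:1.

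The result is "The sample size required was 34 cases in each group, and a total of at least 136 patients needed to be included", and the sentence ends with the claim that this was done "taking into account the 10% dropout rate of the study population". The Abstract, section 2.1 (Study design) and section 2.3 (Randomization, allocation concealment, and blinding) all use the same 136, 34 per group, as the number recruited and randomised. Section 2.8.2 (Analysis methods) places the main analysis at 4 weeks.

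**The concern.** A sample size that includes a 10% dropout allowance should exceed the evaluable number by about one ninth. Here the randomised number equals the evaluable number that the stated inputs require, so the allowance appears to have been mentioned but never applied.

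The test affected is the one the trial is sized on. Whether scalp and intradermal acupuncture act synergistically is a stated aim in the Abstract and the Discussion, and the interaction test is what answers it. If the allowance is missing, the chance of missing a real synergy of the assumed size is understated.

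**Working it through.** **Inputs (all from section 2.4).** Means 41.36, 48.21, 52.87 and 40.54; SD of the interaction 0.96; overall SD 3.38; two-sided alpha 0.05; power 0.90; dropout 10%. The section does not label the means. I take them in the arm order of section 2.1: EG1 (intradermal), EG2 (scalp), EG3 (both), CG (neither).

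**Step 1: reproduce the effect size.**

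- Contrast = 52.87 − 41.36 − 48.21 + 40.54 = 3.84.
- SD of the interaction effects = 3.84 / 4 = 0.96.

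This matches "the standard deviation of the two-factor interaction was 0.96" exactly. It supports the assumed arm order and identifies the calculation as the factorial ANOVA F test for the interaction.

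**Step 2: reproduce the sample size.** Under the noncentral F distribution with df1 = 1 and df2 = N − 4, the noncentrality is λ = N × (0.96/3.38)² = N × 0.08067.

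| Per group | N | λ | Power |
|---|---|---|---|
| 32 | 128 | 10.33 | 0.8904 |
| 33 | 132 | 10.65 | 0.8995 |
| 34 | 136 | 10.97 | 0.9079 |
| 38 | 152 | 12.26 | 0.9356 |

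The smallest equal cell size that reaches 0.90 with complete data is 34, which is the protocol's figure. As a check, the normal approximation gives n = 4 × (3.38 × (1.960 + 1.282) / 3.84)² = 32.6, or 33 per group.

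**Step 3: apply the stated dropout.** 136 × 0.9 = 122.4, so about 122 are evaluable.

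- N = 122: λ = 9.84, power 0.8752.
- N = 120 (30 per group): power 0.8698.
- N = 124 (31 per group): power 0.8805.

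**Step 4: the number that would contain the allowance.** 34 / 0.9 = 37.8, rounded up to 38 per group, 152 in total. That is 152 − 136 = 16 more than planned, or 16/136 = 12%. A 10% loss from 152 leaves about 136, with power 0.908.

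**Step 5: look for another route to 34.**

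- *Rounding of the inputs.* With the 0.96 taken between 0.955 and 0.965 and the 3.38 between 3.375 and 3.385, the complete-data size is 33 or 34 per group, which inflates to 37 or 38. Power at 120 to 124 evaluable never exceeds about 0.885.
- *Normal approximation:* 33, inflating to 37.
- *One-sided 0.05:* 27, inflating to 30.
- *85% power:* 29, inflating to 33. *80% power:* 25, inflating to 28.
- *Main effects:* 17 per group (intradermal) and 3 per group (scalp).

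None of these gives 34 after a 10% allowance.

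**The case against.** The case for leaving the text alone has four parts.

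1. **The 87.5% is a worst case.** Section 2.4 does not say when the 10% is lost. The main analysis is at 4 weeks, participants are inpatients, and follow-up runs to 6 months, so some of the loss may come after the main analysis. This stands: if only part of the 10% is lost by week 4, power lies between 87.5% and 90.8%. It does not make the dropout claim true, because the number still contains no allowance.

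2. **38 per group may be one too many.** The unrounded requirement is about 132 to 133 evaluable in total. With 37 per group (148), a 10% loss leaves about 133 and power 0.902. This stands as a matter of rounding. It depends on counting the loss across the whole trial: 33 complete patients in each cell gives 0.8995. Inflating the required cell size gives 38. Either figure is well above 34.

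3. **The 33/34 boundary is very fine.** An SD of 3.375, which prints as 3.38, takes 33 per group to 0.9003. That is correct, but 33/0.9 still rounds up to 37.

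4. **The shortfall is small, and the analysis is by intention to treat.** The loss is at most about 2.5 points of power, on the interaction alone; both main effects have ample power under the stated means, and type I error is unaffected. This stands as to size. The intention-to-treat principle in section 2.8.1 does not supply 4-week scores for patients who were never assessed, and the protocol's own allowance presumes such losses.

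**Conclusion.** The concern holds. The protocol's 34 per group reproduces exactly as the complete-data requirement for 90% interaction power, and no variant of its inputs gives 34 after a 10% allowance. The statement that 136 covers the dropout is therefore incorrect.

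Power for the interaction is 90.8% with all 136 evaluable and 87.5% with 122 evaluable, so type II error rises to 12.5% against the stated 10%. This rests on the protocol's means and SD being right, on the means being listed in arm order, and, for the 87.5%, on the full 10% being lost before the 4-week analysis and not recovered. The effect is modest and limited to the interaction, but that is the test the trial is sized on.

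**What to change.** Amend section 2.4 to say that 34 per group (136) gives 90.8% power for the interaction with complete data and 87.5% if 10% are lost by the 4-week analysis (122 evaluable), and delete the claim that 136 includes a dropout allowance. This costs one sentence and a slightly less favourable power figure; no extra patients are needed.

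If the sponsor prefers to keep 90% power after 10% loss, recruitment would rise to 38 per group (152), 16 more patients, with the Abstract and sections 2.1 and 2.3 changed to match.

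Adjusting the 4-week comparison for baseline FMA-UE, which is already scheduled, could recover the difference without more patients. If the baseline correlation were 0.3 and 3.38 is an unadjusted SD of post-treatment scores, power at 122 evaluable would be about 0.90. The protocol gives no such correlation and does not say what kind of SD 3.38 is, so this is an option resting on assumptions; the correction to the text does not depend on it.
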